## Abstract

**Background:**

Academic procrastination is a widespread problem among college students. It is linked to poor academic performance and increased college dropout intentions, as well as several mental health problems such as depression, anxiety, and stress. Guided web-based interventions can help reduce procrastination. However, guidance by professional clinicians draws upon valuable and limited societal resources, and a more efficient, scalable form of guidance is needed. Guidance by trained clinical psychology students has not yet been examined.

**Objective:**

The aim of this open trial is to examine the feasibility and acceptability of a web-based procrastination intervention for college students under the guidance of student digital coaches (e-coaches).

**Methods:**

We developed a single-arm trial of a guided web-based intervention targeting procrastination for the Dutch student population. Guidance is delivered by trained clinical psychology students asynchronously in the form of textual feedback on intervention progress, with the aim of supporting and motivating the participant. Participants are recruited at 7 Dutch universities. Primary outcomes are intervention satisfaction, usability, and adherence, which are assessed by the Client Satisfaction Scale (CSQ-8), System Usability Scale (SUS-10), and number of completed modules, respectively. The primary outcomes will be examined by calculating descriptive statistics. Secondary outcomes are e-coach satisfaction and changes to procrastination, depression, stress, and quality of life from pre- to posttest and follow-up.

**Results:**

The project was funded in 2019, and recruitment began in January 2021. As of May 2023, a total of 985 participants were enrolled, of which 372 had completed the posttest and 192 had completed the follow-up. The expected date of analysis and publication of the results is 2024.

**Conclusions:**

The results are expected to contribute to the body of literature regarding eHealth in 3 ways. First, we will examine whether students who procrastinate adhere to and are satisfied with an eHealth intervention targeting this problem. Second, we will explore whether an intervention targeting procrastination can also decrease depression and stress. Lastly, we will investigate whether trained psychology students can effectively guide their peers in web-based interventions. Given the shortage of licensed psychologists, exploring alternative sources of guidance is much needed in order to provide students with the mental health support they need.

**International Registered Report Identifier (IRRID):**

DERR1-10.2196/44907

## Introduction

Academic procrastination is a widespread problem among college students, with studies reporting prevalence rates ranging from 29% to 67% [1-4]. Procrastination, which is defined as the tendency “to voluntarily delay an intended course of action despite expecting to be worse off for the delay” [5], is linked to poor academic performance [6] and increased college dropout intentions [7]. Procrastination is also associated with several mental health problems, such as depression [8], anxiety, stress [9,10], maladaptive coping, and low self-esteem [11]. Negative long-term consequences associated with procrastination include poorer overall health, difficulties with social relationships, financial struggles, and limited career opportunities [10,12,13].

Effective treatments to target procrastination are available. A recent meta-analysis reports that psychological treatments are effective in reducing procrastination [14]. When comparing different types of treatment, cognitive behavioral therapy (CBT) was found to be the most effective in reducing procrastination when compared with self-regulation training, strengths training, and acceptance-based behavior therapy [15].

Still, it is uncommon for students to seek or receive help for mental health complaints due to several barriers. The most common barriers are the perception that help is not needed, as students view their problems as minor or temporary, and a perceived lack of time. Other barriers include a preference for self-management, a fear of stigmatization, and low awareness of available resources [16,17]. Lastly, the detection and treatment of students with mental issues in general is hampered by limited available resources and a limited number of available student psychologists or student counselors, resulting in long waiting lists [18]. One solution to several of these barriers may be eHealth interventions, consisting of web-based treatments such as CBT. They offer quick access to treatment, anonymity, flexibility, and improved cost-effectiveness compared to face-to-face treatment [19,20]. These interventions are effective in improving mental well-being for a wide range of psychological complaints such as depression, anxiety [21,22], and stress [23]. Guided eHealth and face-to-face treatment have been found to be equally effective in treating depression and anxiety [24,25].

Studies examining the effectiveness of eHealth interventions targeting procrastination specifically show that eHealth is also effective in reducing procrastination [26-28]. When comparing eHealth to traditional treatment, chat-based counseling and face-to-face counseling resulted in a comparable decrease in procrastination [29]. Similarly, a group intervention and self-guided internet-based treatment produced comparable levels of improvement for procrastination behavior after the treatment period [30].

However, there are also drawbacks to eHealth. An often-mentioned reason for a lessened intervention effect is the problem of nonadherence, meaning participants do not make optimal use of the intervention [31-33]. For procrastination specifically, the problem of nonadherence could be exacerbated, as individuals with procrastination tendencies can struggle to adhere to the treatment [28].

Adding therapist guidance to eHealth interventions could offer a solution to this problem. Meta-analytic evidence suggests that guidance from professionals increases eHealth treatment effectiveness when compared with unguided treatment [24,34]. This may be explained by the positive effect guidance has on motivation, engagement, and adherence [35-37]. However, the addition of professional guidance in eHealth draws upon valuable and limited societal resources, and there is a scarcity of properly trained professionals.

The question arises whether there is a more efficient, scalable form of guidance without lowering therapy effectiveness. There is evidence suggesting guidance by nonclinicians (eg, peers, research assistants, or other laypeople) has comparable effects compared to guidance by clinicians in eHealth interventions [38]. What has not specifically been examined yet is whether guidance by trained clinical psychology university students can be equally effective. Were this to be the case, it could greatly reduce the load on the health care system as trained clinical psychology students could offer eHealth guidance for significantly lower costs compared to clinicians. Finally, most clinical psychology students welcome the opportunity to gain hands-on experience guiding real clients during their studies.

The main objective of this study is to evaluate the acceptability and feasibility of a new eHealth intervention targeting procrastination in college students that is guided by clinical psychology students by assessing its usability, adherence, and client satisfaction. The secondary objectives are to explore differences between pre- and posttests for procrastination, depression, stress, and quality of life.

## Methods

### Study Design

This study is a single-arm open trial of a guided eHealth intervention (GetStarted) aimed at decreasing procrastination in college students. It uses a single-group pretest (T0), posttest (T1), and follow-up (T2) design in which T1 and T2 are administered 4 weeks and 6 months after T0, respectively. The study is conducted within the Caring Universities consortium, a Dutch project that is part of the World Mental Health International College Student Initiative (WMH-ICS) of the World Health Organization (WHO) [39].

### Participants and Recruitment

Participants are undergraduate, graduate, or PhD students enrolled in the abovementioned 7 universities across the Netherlands. These 7 universities are situated in 10 cities across the Netherlands and have a combined total of approximately 190,000 domestic and international students. Participants may be both domestic and international students.

The aim of this study is to recruit a minimum of 50 students, and recruitment is conducted in 3 ways. Firs, through a yearly web-based survey of the WMH-ICS. This survey canvasses the mental well-being of students and is sent by email to all the students of the participating universities. At the end of the survey, students who want to receive feedback are provided feedback on their mental health. Students who show increased procrastination tendencies (ie, a score >28 on the Irrational Procrastination Scale; IPS) are invited to sign up for the Caring Universities procrastination program. Second, marketing activities are conducted on the web through social media and on campus through posters, flyers, and other advertisements. Third, we recruit participants through the staff at participating universities. Staff members who work directly with students, such as student psychologists, study advisors, and lecturers, are informed of the program and can recommend it to students who might be interested.

Students are not offered compensation for participation.

### Eligibility Criteria

Participants will be included if they meet the following criteria: (1) being aged 16 years or older; (2) being enrolled as a bachelor, master’s, or PhD student; and (3) having given informed consent.

The sole exclusion criterion is suicidal risk. Participants will be asked if they have had thoughts of killing themselves or made plans to kill themselves in the past 12 months. If they answer yes, the follow-up question, “How likely do you think it is that you will act on this plan in the next 12 months?” is asked. Participants that respond to this question with “somewhat likely” or “very likely” are excluded from the intervention.

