### Possible Harms

Several meta-analyses show that internet-based programs might be beneficial for college students [41] and that there are no indicated risks to internet-based programs. Moreover, individual patient data meta-analyses showed that participants who received an internet-based program for depression had a lower risk of clinical deterioration when compared with the control group [20,42]. These findings seem to indicate minimal to no risk of possible harm. However, in the event that a participant shows signs of more severe mental health problems, which include but are not limited to self-harm or suicidality, in their responses to the questions in the intervention, the protocol for (emerging) crisis situations will be applied: the e-coach (under the supervision of and in collaboration with a certified mental health care psychologist) will reach out and assess the student’s current situation in more detail through the platform. In cases of mild to moderate risk of a worsening of psychological symptoms, we will advise the student to seek professional help aside from participating in the study. In cases of high risk, we advise the student to seek out professional help and resolve the current situation before continuing participation in the study.

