#### Assessments

An overview of the assessments can be seen in Table 1.

**Table 1 table1:** Measures and assessment points.

Measures	Assessment points		
	T0^a^	T1^b^	T2^c^
Sociodemographic	✓		
Client Satisfaction Questionnaire (CSQ-8)		✓	
System Usability Scale (SUS-10)		✓	
Irrational Procrastination Scale (IPS)	✓	✓	✓
Perceived Stress Scale (PSS-10)	✓	✓	✓
Patient Health Questionnaire (PHQ-9)	✓	✓	✓
The Mental Health Quality of Life Questionnaire (MHQoL)	✓	✓	✓

^a^Pretest.

^b^Posttest (4 weeks).

^c^Follow-up (6 months).

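### The suicidal-risk screen opens on thoughts or plans, but the item that decides exclusion asks only about a plan, so it does not clearly fit students with thoughts and no plan

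*Protocol article*

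**What the plan says.** The protocol article, under Eligibility Criteria, states: "The sole exclusion criterion is suicidal risk". The screen has three steps.

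- **Opening question**, described in the article's own words: "Participants will be asked if they have had thoughts of killing themselves or made plans to kill themselves in the past 12 months".
- **Follow-up**, introduced by "If they answer yes, the follow-up question" and given as a quoted item: "How likely do you think it is that you will act on this plan in the next 12 months".
- **Decision rule**: a reply of *somewhat likely* or *very likely* to that item excludes the student from the intervention. No other reply is named.

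Under Possible Harms, a separate procedure applies once a student is taking part. It starts when a participant "shows signs of more severe mental health problems, which include but are not limited to self-harm or suicidality". The trigger is what participants write: "in their responses to the questions in the intervention, the protocol for (emerging) crisis situations will be applied". The e-coach then assesses the situation under the supervision of a certified psychologist. High-risk students are advised to seek professional help and "resolve the current situation before continuing participation in the study".

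**The concern.** The opening question and the deciding question cover different groups. The first takes in students with suicidal thoughts, with plans, or with both. The second speaks only of a plan. A student who has thoughts but has made no plan answers yes at the first step and then meets a question about something they have not reported.

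This is the only exclusion criterion and the only entry safety rule that the article describes. It is applied to students from the age of 16 who register themselves online. If the wording leads such a student to give a low answer despite believing that they may act, they enter a low-intensity procrastination programme that the criterion was meant to keep them out of. What is at stake is the safety of individual students. The estimates of satisfaction, usability and adherence do not depend on it.

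**Working it through.** There is no figure in the plan to reproduce. The check is to follow each kind of student through the rule as printed, and then to look for another entry rule that would cover the gap.

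**Following the rule**

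1. *No thoughts and no plan.* The answer is no, there is no follow-up, and the student enters. The rule works.
2. *A plan, with or without separate thoughts.* The answer is yes, and the follow-up refers to something the student has reported. The student is excluded at *somewhat likely* or *very likely*. The rule works.
3. *Thoughts without a plan.* The answer is yes, so on a literal reading the follow-up is asked. The plan it mentions has no counterpart in what the student reported. Three responses are possible:
   - The student reads the item generously, as meaning the thoughts just endorsed, and answers by their real likelihood of acting. The rule then works.
   - The student reads it literally and gives a low answer because there is no plan. The student enters, whatever they think about acting.
   - The student leaves it blank, if the platform permits that. No excluding answer is given, so under the printed rule the student enters.

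   The article does not say which of these happens.

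**Looking for another entry rule**

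- The PHQ-9 is taken at T0 according to Table 1, but it is listed as a secondary outcome. No score on it is tied to eligibility.
- The procedure under Possible Harms needs no plan to be triggered, so it does reach thoughts-only students. It starts only after entry, and only if signs appear in their answers to the modules, which concern procrastination.
- No other section gives an entry rule for this group.

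**Size**

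The number wrongly admitted would be

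(students screened) × (share with thoughts but no plan) × (share of those who think it at least somewhat likely that they will act) × (share of those who answer below the cut-off because of the wording).

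The article gives none of these four terms. The 985 enrolled by May 2023 (Results section) are students who passed the screen, and that count says nothing about the three shares. No range is offered, because any range would rest on invented inputs.

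**The case against.** The strongest reply is that the harm path is narrow and rests on an instrument that we cannot see. The student must have thoughts without a plan, must privately judge acting to be at least somewhat likely, and must still answer low because of one word. The article paraphrases the opening question. The live screener may hold separate items on thoughts and on plans, with its own branching. Excluding on stated likelihood of acting, and not on thoughts alone, is also a defensible threshold for a programme of this kind. A wider trigger for monitoring after entry does not contradict it. The safeguards after entry are real: e-coaches read participants' answers and give feedback after each completed module, a research team member monitors the coaching, and a certified psychologist supervises any crisis assessment.

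Much of this stands, and it limits the point. A reader might infer that thoughts-only students are asked nothing about how likely they are to act. The text does not support that: read literally, any yes leads to the follow-up, so they are asked a question that fits them badly. They would get no likelihood question only if the item appeared solely after a plan was endorsed, and the article does not say so. Nor do the documents show that the live screener is faulty, that at-risk students have in fact been admitted, or that thoughts alone ought to exclude.

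What the reply does not remove is the mismatch in the printed rule. The follow-up is given as a quotation, it decides the sole exclusion, and its wording is narrower than the question that leads to it. A safety screen that students complete themselves should not depend on a generous reading.

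**Conclusion.** The point holds as a minor safety improvement. As printed, the deciding item does not clearly apply to students who report suicidal thoughts without a plan, and such a student could fall below the exclusion cut-off despite thinking it likely that they will act. The conclusion assumes that the quoted item is the one in use and that no separate likelihood item exists for this group. How these students would answer and how many there are remain unknown, and the number could be very small. The crisis procedure softens the consequence but does not repair the entry rule. The primary outcomes and their success thresholds (a mean CSQ-8 of at least 24, a mean SUS-10 of at least 70, adherence of 50%) are untouched.

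**What to change.** For students still to be screened, change the follow-up so that it asks how likely they are to act on *these thoughts or this plan* in the next 12 months. Show it to everyone who answers yes at the opening question. Keep the present cut-off at *somewhat likely* and *very likely*, and record whether thoughts, a plan or both were endorsed. If the platform already puts a suitable likelihood question to thoughts-only students, the screener needs no change and the Eligibility Criteria text should describe that route.

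The cost is the wording of one online item and one extra recorded field. There are two downsides. The item will differ between earlier and later enrolees, so the date of the change should be reported. A few thoughts-only students who rate themselves somewhat or very likely to act will be newly excluded, as the criterion intends. Students already enrolled are not re-screened. The change is still useful because the Sample Size section expects the intervention to stay open for several years, although some of those screened later may fall outside the trial's own analysis, which is expected in 2024.

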### Intervention

The guided eHealth program aimed at reducing procrastination behavior (GetStarted) is developed based on the principles of CBT. Students are involved in the development of the program by giving their opinions and feedback on the program content as well as the layout of the website that contains the program. The feedback is implemented to ensure that GetStarted meets students’ needs and preferences.

GetStarted (Figure 1) consists of 9 modules, of which 5 are mandatory main modules and 4 are optional modules. The modules consist of psychoeducation, reflective questions, interactive exercises, and homework assignments. The content is delivered both textually and visually, including through the use of pictures, infographics, and videos. Each module takes approximately 30 to 45 minutes to complete, and students are advised to complete 1 main module a week. The duration of the program will therefore be approximately 4-5 weeks, though students are allowed to go at their own pace and can access the intervention for 2 years. Students will be able to access the program from any device that allows internet access.

The first module offers an introduction to the program and its contents. Students are recommended to continue with the second module right away, which covers information on the psychological processes behind procrastination. The third module will allow students to identify the negative thoughts and feelings that accompany certain tasks, causing them to procrastinate. The fourth module will contain a cognitive restructuring exercise in which they will challenge their negative thinking patterns. The fifth and final main module will let the student reflect on their progress, prepare for the future, and include a summary of all the modules.

**Figure 1 figure1:**
[figure not shown]
Screenshot of GetStarted, an eHealth intervention targeting procrastination.

In addition to the main modules, students will be able to choose to do 1 or several of 4 optional modules. The topics of the optional modules will be (1) breaking a big task into smaller parts; (2) creating and sticking to a plan; (3) motivational techniques; and (4) increased productivity. All optional modules will become available upon completion of the second main module.

The intervention will be created based on the following principles of optimized user interface [40] in collaboration with a user experience designer: a menu containing several main sections, presentation of content in small chunks, stepwise exercises with separate instructions at each step, examples presented in expandable containers, and showing responses given by the participant in previous exercises when relevant.

### Digital Coaches

During the registration process, participants select a digital coach (ie, e-coach) to support them during the program. The e-coach provides asynchronous, textual feedback through the platform after the completion of every module by the participant. While doing the intervention, participants respond to questions about the subject of procrastination. The e-coaches read these answers, which form the basis of the textual feedback. In this feedback, e-coaches respond to the participant’s answers, show empathy, encourage the participant to apply the techniques, and ask reflective questions with the aim of deepening the participant’s understanding of their procrastination. The feedback contains the following elements:

an opening statement containing positive feedback for the participant’s completion of the module;selecting 2 to 3 points of note in the participant’s answers to provide empathy, encouragement, reiterate the goal of the module, or ask a follow-up question; anda closing statement regarding the next module.

Writing feedback for a single module takes around 30 minutes on average, and e-coaches provide feedback within 3 working days of a module being completed by the participant. E-coaches also send reminders about the intervention to participants who have been inactive for a while. E-coaches who cannot provide feedback within 3 working days due to a short temporary absence (such as a holiday) write an explanatory message to the participants explaining the absence and informing them of a return date. In the event that an e-coach cannot adequately perform their duties in the long term, the participant is assigned a different available e-coach. The reason for the change, as well as an apology, are provided to the participant by the new e-coach. A member of the research team monitors the e-coaches and the quality of the coaching.

E-coaches are (research) master students in clinical psychology and third-year clinical psychology bachelor students who meet a number of requirements in the area of low-intensity treatments for common mental health problems. E-coaches are recruited by making third-year bachelor and master students aware of the opportunity to coach as an (extracurricular) internship. They can apply for the position with their curriculum vitae and motivation. Based on their previous experience and motivation, certain students are then invited for an interview with the research team, and selected students are offered the position. These students complete 6 hours of coach training before starting their coaching activities and are required to attend weekly 1-hour intervision meetings, which are supervised by the research team.

